##### Acceptability

The acceptability of the digitally supported mindfulness intervention will be operationalized as perceived usefulness through 4 separate questions such as “How useful do you rate the [app/online workshop/workbook/all in all]?” We will use a 5-point Likert scale (1=not at all applicable to 5=very applicable). We will assess which of the nursing-specific courses were helpful (listing of the names of the nursing-specific courses; multiple answers possible).

##### Intensity of Intervention Use

App use will be measured through previous experience with the app (“yes, I have tried out the app”; “yes, I use the app regularly”; or “no, I have never used the app”), previous experience with the app before code activation (“yes, I have tried out the app”; “yes, I use the app regularly”; or “no, I have never used the app”), date of access code activation (yes [date of activation] or no), total amount of app-based meditation (in minutes), total number of app-based meditation exercises, subjective assessment of app use frequency (several times a day, daily, 4-6 times per week, 1-3 times per week, less than once a week, or never), time of use (in my free time, before my shift, during my shift, during my breaks on shift, or after my shift), and use of the app-based nursing-specific courses (list of nursing-specific courses; selection of multiple answers).

Participation in the 2 user-engaging components (web-based workshop and workbook) will be assessed using a binary variable (yes or no). Frequency of workbook use will be assessed using the following answer options: several times a day, daily, 4 to 6 times per week, 1 to 3 times per week, less than once per week, or never. Finally, we will assess for non–app-based meditation (yes or no).

#### Sample Size

On the basis of the available literature on interventions similar to ours, we assumed a medium effect size (Cohen *d*=−0.67) in reducing stress measured by PSS-10 [44]. The sample size calculation was conducted for a 2-tailed *t* test with a significance level of α=.05 and a power of β=.80 (comparison between the IG and the WCG). Sample size calculations using the G*Power tool (Düsseldorf University) suggested that 72 participants (36 in the IG and 36 in the WCG) are needed to detect an effect size of 0.67. Assuming a dropout rate of 20%, 18 additional participants were required (45 per group).

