As regular (preferably daily) practice is considered a prerequisite for efficacy [18], heterogeneous results may stem from a lack of acceptance of digitally supported mindfulness interventions, which leads to insufficient or infrequent meditation practice. High dropout rates present a prevalent problem in digitally supported mindfulness intervention research, with dropout rates ranging from approximately 25% [21] to approximately 48% [20]. Nonadherence in intervention instructions or dropout may occur when demanding work schedules and time constraints prevent participants from engaging in meditation practice to a degree that is necessary to achieve desirable outcomes. International differences in health care systems and cultural norms may also influence interest and participation in specific interventions on a regular basis [15].

To decrease dropouts and increase meditation practice, variables related to adherence and acceptability should be investigated [22]. This study distinguishes between adherence and acceptability. Adherence refers to the degree to which participants follow a treatment protocol [24], such as instructions regarding the frequency of meditation practice. Acceptability refers to the factors influencing digitally supported mindfulness intervention use.

In addition, steps should be taken to provide participants with engaging interventions to further treatment adherence and limit dropout risk, which could be achieved by adding user-engaging elements such as web-based workshops and workbooks. Mindfulness workbooks with writing exercises can be effective in stress reduction [25,26] and can be easily used by individuals with limited technological affinity. Previous research suggests that social interactions may enhance the efficacy of digitally supported interventions [15]; for example, studies on individuals with depression found digital interventions to be significantly more effective in reducing depressive symptoms when the intervention was guided by a mental health professional [26,27]. In addition, providing participants with the opportunity to share their experience with the intervention app in a web-based workshop setting could limit dropout risk [20].

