#### Recruitment

Recruitment took place between August and October 2021 during hospital staff meetings, as well as during web-based meetings among project partners, which were attended by nurses. In addition, participants were recruited via weekly newsletters, handbills, and flyers handed out at participating hospitals and nursing schools.

Eligible nurses and nursing trainees interested in participating in the study were able to register via a website and were emailed the link to the time point 0 (T0) survey (baseline survey). Upon obtaining informed consent, participants were prompted to fill out the web-based survey. Information regarding the study design was not disclosed to the participants.

Informed consent was obtained from all participants before the start of each web-based survey. Informed consent materials are currently available only in German (Multimedia Appendix 1). To prevent individuals from participating more than once, we checked for duplicates in the first and last names and email addresses during registration. Each registered person received personalized invitation letters via email with an individual access key to the survey (token).

Incentives for study registration and survey participation were available at the discretion of each hospital’s management, thus varying across locations. A raffle was initiated by the intervention provider at one of the hospitals to incentivize staff participation in the surveys. Incentives included 15 gift cards €15 (US $15.8) each for various shopping websites for the first 2 surveys, whereas the last survey was incentivized by the opportunity to win 1 of the 10 gift cards €30 (US $31.6) each. At some participating hospitals, participants were allowed to participate during work hours, whereas others required their staff to partake during their personal time.

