## Results

Data collection at T0 was conducted from the end of September 2021 until October 2021. At the end of October 2021, a total of 79 individuals were randomized to either the IG (40/79, 51%) or WCG (39/79, 49%). All data collection will be completed by the beginning of August 2022. Data analyses will begin after data collection and will be completed by December 2022.

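### The plan requires 90 randomized participants for 80% power, but 79 were randomized; at its own 20% dropout the power is about 74%

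*Protocol article*

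**What the plan says.** The Sample Size section starts from the literature: "we assumed a medium effect size (Cohen *d*=−0.67) in reducing stress measured by PSS-10". It then fixes the test, "The sample size calculation was conducted for a 2-tailed *t* test with a significance level of α=.05", and the target, "a power of β=.80 (comparison between the IG and the WCG"); β here is evidently a slip for 1 − β. The result is that G*Power "suggested that 72 participants (36 in the IG and 36 in the WCG) are needed to detect an effect size of 0.67". The allowance for loss follows: "Assuming a dropout rate of 20%, 18 additional participants were required (45 per group").

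The Recruitment section describes enrolment in the past tense: "Recruitment took place between August and October 2021". The Results section gives the outcome at the end of October 2021: "a total of 79 individuals were randomized to either the IG (40/79, 51%) or WCG (39/79, 49"%).

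On expected loss, the Introduction (Digitally Supported Mindfulness Interventions) calls high dropout a common problem in this field, "with dropout rates ranging from approximately 25% [21] to approximately 48% [20"). The Sample Size section gives no reason for assuming 20%.

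The primary analysis (Research Question 1) is a two-sample t test on T0-to-T1 difference scores. The intention-to-treat set is all randomized participants, with imputation of missing data.

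**The concern.** The article prints a requirement of 90 and an achieved number of 79, and leaves the 80% power as the only statement about the trial's sensitivity. A reader who takes the Sample Size section at face value will credit the trial with a power that it has only if loss is much lower than the plan assumes.

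This matters most if the primary test is not significant. The T0-to-T1 comparison of perceived stress is the only randomized between-group test of the primary outcome. Research Question 1 calculates Cohen d only when P < .05, so a null result would come without a planned effect size. The stated 80% power for d = 0.67 would be what readers have to judge it by, and they could over-read it as evidence against an effect of that size.

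**Working it through.** **Inputs.** From Sample Size: d = 0.67, two-sided α = .05, target power 0.80, 36 evaluable per group, 20% dropout, 45 per group randomized. From Results: 40 and 39 randomized. From the Introduction: dropout of about 25% and about 48% in comparable studies.

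**Formula.** For group sizes n1 and n2, the degrees of freedom are n1 + n2 − 2 and the noncentrality is δ = d·√(n1·n2/(n1 + n2)). Power is the probability that a noncentral t variable with noncentrality δ exceeds the two-sided 5% critical value (the opposite tail is negligible).

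**1. The plan's own figures reproduce.**
- 36 v 36: δ = 0.67 × √18 = 2.843, 70 df, power 0.8005.
- 35 v 35: power 0.789. So 36 is the smallest group size that reaches 0.80.
- Inflation: 72/(1 − 0.20) = 90, or 45 per group, which is 18 more.

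**2. The shortfall.**
- 90 − 79 = 11, or 12% of the requirement.
- 79 × 0.80 = 63.2 expected evaluable, against the 72 needed.
- Largest loss that still leaves 72: 1 − 72/79 = 8.9%.

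**3. Power with 79 randomized.** Each group is reduced by the dropout rate and rounded.

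| Dropout | Evaluable | δ at d = 0.67 | Power at d = 0.67 | d detectable with 80% power |
|---|---|---|---|---|
| 0% | 40 v 39 | 2.977 | 0.836 | 0.64 |
| 8.9% | 36 v 36 | 2.843 | 0.8005 | 0.67 |
| 20% (plan) | 32 v 31 | 2.659 | 0.744 | 0.72 |
| 25% (Introduction, low end) | 30 v 29 | 2.573 | 0.715 | 0.74 |
| 48% (Introduction, high end) | 21 v 20 | 2.144 | 0.552 | 0.90 |

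At the plan's own dropout rate the type II error is 1 − 0.744 = 25.6%, where 20% was intended. Across the cited range it is 28.5% to 44.8%.

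**The case against.** The strongest reply is that nothing in the Sample Size section is miscalculated. It reports an a priori calculation in the past tense, and the article does not say that 79 gives 80% power. The 79 is disclosed, and the Strengths and Limitations section twice calls the trial small. This stands in part: the fault is an unreconciled shortfall and not an arithmetic slip. But the remarks on size explain the absence of a third arm and the risk of chance imbalance. Neither addresses power.

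A second reply is that 79 exceeds 72, so power could reach 0.836 if every T1 score is observed. The article also does not say whether its 20% is loss by T1 or over the whole follow-up. If it is the latter, loss at T1 would be lower; about 15% (34 v 33) would give 0.771. This is a fair caveat. Still, the 20% is applied directly to the calculation for the between-group test, so reading it as loss for that test is natural. Analysing all 79 with imputation does not close the gap, because imputation does not recover the information in unobserved T1 scores.

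Third, the 25% to 48% range comes from two cited studies whose definitions of dropout are not given, and this trial uses workshops, a workbook, reminders and some incentives to limit loss. So 20% is optimistic and unexplained but does not contradict the text, and the 48% row is an unfavourable extreme.

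Finally, the cost at 20% dropout is moderate, about 6 percentage points of power. Type I error and the validity of the estimate are untouched. That is true, and it is why the remedy is restricted to reporting.

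**Conclusion.** The concern holds. The sample size derivation is correct, but the enrolled trial does not meet it, and the article leaves the 80% figure unrevised. On the plan's own assumptions (d = 0.67, two-sided .05, 20% dropout bearing on the T0-to-T1 comparison), power is about 74% and the effect detectable with 80% power is d = 0.72. The stated power survives only if loss is at most 8.9%, less than half of what the plan assumes. At the dropout rates cited in the Introduction, power would be about 72% to 55%, with detectable effects of 0.74 to 0.90.

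These figures assume that missing T1 scores are lost information for the primary test and that loss is about equal in the two groups. The per-protocol analysis, limited to completers who report adherence, will not have more power and probably has less.

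**What to change.** Leave enrolment, the test and the analysis sets as they are. In the Sample Size section, add that 79 participants were randomized against the 90 required, so that the t test has about 74% power for d = 0.67 at 20% dropout (72% at 25%, 55% at 48%), with effects of d = 0.72 (0.74, 0.90) detectable with 80% power. If the 20% was meant as loss over the whole follow-up, say so and give the loss expected at T1.

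A further sentence is advisable, though the correction does not depend on it: a non-significant primary result will be read from its 95% confidence interval and not as absence of an effect.

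The cost is about two sentences and a less favourable stated power. By the article's own timetable, analysis starts only after data collection ends in August 2022, so the text can be corrected before any result is known.

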#### Statistical Methods

##### Overview

Analyses will be conducted using *SPSS Statistics* (IBM)*.* For tests involving our primary outcome variable, we will set an α level of .05. For all other analyses, to reduce α-error inflation, we will interpret the obtained *P* values descriptively, meaning all other analyses will be exploratory and are designed to observe trends and not to identify significance.

Patterns of missing data will be assessed, and adequate data imputation techniques such as multiple imputation with *SPSS Statistics* (IBM) will be applied. Before doing so, we will assess the percentage of missing data. We will also use Little's Missing Completely At Random test to determine patterns of missing data (ie, missing completely at random vs not missing at random).

We will reverse code 3 outcomes [32,38,40] so that a higher score indicates health improvement. For example, the scale assessing burnout [40] is designed to indicate that a score of 1 indicates a rather minuscule risk of burnout, whereas a score of 100 indicates the highest risk of burnout, meaning that greater scores indicate a worsening of symptoms. After recoding this variable, greater scores will reflect a lower risk of burnout (ie, an improvement in symptoms).

Effectiveness will be evaluated using an intention-to-treat (ITT) approach; all randomized participants will be included in our analyses [45].

Efficacy will be evaluated using a per-protocol (PP) approach; only study completers who report adherence will be included in our analyses.

Several analyses will be used to address the research questions. To ensure that our randomization has worked as intended, we will assess for between-group differences for relevant participant characteristics and, if needed, adjust the following analyses. For research questions 2, 3, and 4, we will create a pooled data set merging the data of the IG and the WCG. We will merge the data of the 2 groups so that IG T0 data will be combined with WCG T1 data, and IG T1 data will be combined with WCG T2 data, as described in Textbox 1. For research questions 3 and 4, relationships between variables will be examined using correlation analyses (Pearson correlation coefficient, eta quotient, and chi-square tests). If violations of the assumptions associated with any of the analyses are detected, alternative tests will be used.

Data pooling procedure.

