#### Outcomes

The German version of each questionnaire has been previously validated. All outcomes of interest consist of continuous variables based on self-report data. Our primary outcome will be perceived stress measured using the 10-item Perceived Stress Scale (PSS-10) [32]. Secondary outcomes will include sense of happiness (Likert scale) [33], life satisfaction (L-1) [34], mindfulness (Five Facet Mindfulness Questionnaire) [35], well-being (World Health Organization-Five Well-Being Index) [36], self-care (Hamburg Self-Care Questionnaire; only pacing scale) [37], pain intensity (numerical rating scale 0-10) [38], work-related sense of coherence questionnaire [39], burnout (Copenhagen Burnout Inventory; work-related burnout scale and client-related burnout scale) [40], job satisfaction (Warr-Cook-Wall Scale [41], modified by Cooper et al [42]), and work engagement (Utrecht Work Engagement Scale) [43].

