**Newly pooled data set and data included**
Participant data baselineCases of the intervention group at time point 0Cases of the wait-list control group at time point 1Participant data 10 weeks after intervention startCases of the intervention group at time point 1Cases of the wait-list control group at time point 2Participant data 24 weeks after intervention startCases of the intervention group at time point 2Cases of the wait-list control group at time point 3

##### Research Question 1

We will present the ITT sample’s baseline characteristics and test for detectable between-group differences. For continuous variables, mean, SD, median, minimum, and maximum values will be calculated. For categorical variables, frequencies (absolute and percentages) will be calculated.

To evaluate the effectiveness and efficacy of the 10-week access, we will create one difference score per group for each of our outcomes assessed at T0 and T1. Using a 2-sample *t* test, we will test whether significant differences exist between the 2 difference scores in the IG and WCG. We will perform this for the ITT and PP sample. If *P*<.05, Cohen *d* will be calculated.

##### Research Question 2

To evaluate long-term effectiveness and efficacy, we will use the pooled data set. To analyze the effect of time on our variables of interest, a repeated-measures ANOVA will be conducted for each of our outcomes. As only participants randomized to the IG will be assessed at 38 weeks after allocation, long-term efficacy within this group will be examined using an additional repeated-measures ANOVA.

Using a PP approach, we will examine the relationship between *app-based minutes of meditation* and each previously calculated difference score using the pooled data set. Linear regression will be performed to examine the relationship between the minutes of meditation and each outcome. The baseline scores of primary and secondary outcomes will be entered into the model as additional explanatory variables to control for individual differences before the start of the intervention.

##### Research Question 3

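### The .05 level is given to every PSS-10 test rather than to one designated test, so per-protocol, pre-post and regression results on stress can also be declared significant

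*Protocol article*

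**What the plan says.** The Outcomes section names the measure: "Our primary outcome will be perceived stress measured using the 10-item Perceived Stress Scale (PSS-10"). It attaches no time point, analysis set or test.

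The Overview of the Statistical Methods then sets the error rule: "For tests involving our primary outcome variable, we will set an α level of .05". The remainder is treated differently: "For all other analyses, to reduce α-error inflation, we will interpret the obtained *P* values descriptively".

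The later sections plan these tests on PSS-10:

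- **Research Question 1:** a two-sample t test of the T0–T1 difference scores, IG against WCG. "We will perform this for the ITT and PP sample".
- **Research Question 2, pooled data:** a repeated-measures ANOVA for time, introduced as addressing both long-term effectiveness (ITT) and long-term efficacy (PP).
- **Research Question 2, IG only:** "long-term efficacy within this group will be examined using an additional repeated-measures ANOVA".
- **Research Question 2, PP:** a linear regression of the change scores on app minutes, with baseline scores as covariates.
- **Sensitivity Analyses:** complete-case repeats of Research Questions 1 and 2.

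The Sample Size section rests on one test: "The sample size calculation was conducted for a 2-tailed *t* test with a significance level of α=.05 and a power of β=.80", described as a "comparison between the IG and the WCG".

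**The concern.** The dividing line is the outcome variable, so any test with PSS-10 in it keeps the .05 level. The article neither ranks these tests nor adjusts among them. Only one of them is both randomized and powered.

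The others support weaker conclusions. The PP t test drops the protection of randomization: under Table 1, adherence at T1 is recorded in the IG only, so the selection falls on one arm. The pooled and IG-only ANOVAs test change over time without a concurrent control. The regression relates self-selected meditation time to change.

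Under the rule as written, a null randomized comparison could stand beside a significant finding on the primary outcome from one of these tests, and the plan gives no ground for ranking the first above the second.

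**Working it through.** **1. The plan's own figure.** Inputs from Sample Size: d = 0.67, two-sided α = .05, power .80, 1:1 allocation. With n per group, the noncentrality is δ = d·√(n/2) on 2n − 2 degrees of freedom. At n = 36, δ = 0.67 × √18 = 2.84 on 70 df. The noncentral t gives power 0.789 at n = 35 and 0.8005 at n = 36. So 36 per group (72) reproduces. Dropout: 36/0.80 = 45 per group (90) also reproduces. The calculation is sound for one IG v WCG t test at .05, and for that test only.

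**2. Which tests to count.**

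- *Four tests:* ITT t test, PP t test, one pooled ANOVA, one regression.
- *Six tests:* the same, plus the pooled ANOVA in PP and the IG-only ANOVA in PP.

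The IG-only ANOVA is counted in PP alone, because the article calls it efficacy and defines efficacy as PP. Running the pooled ANOVA in both sets is inferred from its description as addressing effectiveness and efficacy. Complete-case repeats are sensitivity checks and are not counted.

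**3. Independence benchmark.** The chance of at least one P<.05 is 1 − 0.95^k.

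- k = 2: 1 − 0.9025 = 9.8%
- k = 4: 1 − 0.8145 = 18.5%
- k = 6: 1 − 0.7351 = 26.5%

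The tests share data, so the true figures are lower.

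**4. Simulation under the complete null.** From the documents: 40 IG and 39 WCG randomized (Results), four waves, and pooling of IG T0/T1/T2 with WCG T1/T2/T3. The 80% completion follows the 20% planning dropout. Assumed, because the documents do not give them: within-person correlation 0.3, 0.5 or 0.7; adherence among completers 35%, 60% or 85%; minutes unrelated to outcome. ITT uses all 79. The PP t test compares adherent IG completers with WCG completers. There were 4,000 to 6,000 simulated trials per setting.

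| PSS-10 tests at .05 | Chance of at least one P<.05 |
|---|---|
| ITT t test alone | about 5% |
| ITT and PP t tests | about 6–9% |
| Four tests | about 14–17% |
| Six tests | about 19–22% |

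The correlation hardly matters, because every test works on within-person change. Lower adherence pushes the figures towards the upper end.

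**5. A separate point: drift.** If stress shifts by an assumed 0.1 SD per wave in everyone and the intervention does nothing (correlation 0.5, adherence 60%), the pooled ANOVA in ITT is significant in about 33% of trials. The randomized ITT test stays near 5%. The drift value is illustrative only.

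**The case against.** The strongest reply is that the main comparison can be identified. The trial is powered on an IG v WCG t test on PSS-10, and Research Question 1 contains the only such test. That question is set at 10 weeks, and T1 is the only follow-up wave before the WCG starts the intervention. This stands. A reader might infer that the trial has no main comparison at all; the documents do not support that. What is missing is a sentence that confines the .05 level to this test and chooses ITT over PP.

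Second, the clause about reducing alpha inflation is attached to the non-PSS-10 analyses, which include a long list of secondary outcomes, and there the rule does its work. So it would be unfair to say that the plan breaks a promise about PSS-10. The rule simply leaves those tests uncontrolled.

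Third, a reader might add the drift results to the error rate and quote a much larger figure. That is not a type I error: with drift, the hypothesis of no change over time is false, and rejecting it is correct. The fault there is confounding, which exists with a single test and is not cured by multiplicity control.

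Fourth, Research Questions 1 and 2 differ, and family-wise control across different questions is partly a matter of judgement. The article does not say that it would let a Research Question 2 result stand in for a null Research Question 1 result. That is fair, but all these tests carry the primary-outcome label and the same threshold, so nothing in the rule prevents it.

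Last, a separate analysis plan could set a hierarchy. It could, but the article states a rule rather than staying silent, and that rule would have to be overridden.

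**Conclusion.** The concern holds in this form: the article gives the .05 level to every PSS-10 test, while the design supports it for one. Under a complete null, the chance of at least one nominally significant PSS-10 result is roughly three times the nominal level for four tests (about 14–17%) and roughly four times for six (about 19–22%). The ITT and PP t tests alone account for little of this (about 6–9%); most comes from the Research Question 2 tests.

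That the rule covers these tests follows directly from the text. The size is less certain: it rests on the count of tests and on assumed completion, correlation and adherence. The lack of a concurrent control in the Research Question 2 time tests is a further reason not to treat them as confirmatory, but it is a matter of bias and adds nothing to these percentages.

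**What to change.** Replace the sentence on the α level with: *The single confirmatory test is the ITT comparison of IG v WCG in T0–T1 (10-week) PSS-10 change, two-sided alpha .05; all other PSS-10 tests (PP, Research Question 2, sensitivity) are exploratory and reported as estimates with 95% CIs.*

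This matches the test on which the sample size was based. The planned 36 analysed per group still gives 80.05% power at d = 0.67, so N does not change. The article schedules the analyses after data collection ends, so the sentence can be fixed before they start.

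The price is that long-term and PP results on PSS-10 can no longer be called significant. The alternative, keeping several confirmatory tests with a Bonferroni split, costs more: for the IG v WCG test, power at 36 per group falls to 70.9% with two tests, 61.1% with four and 55.3% with six. Restoring 80% would need 44, 52 or 56 per group before dropout.

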## Methods

### Design

We will conduct a multicenter RCT with a WCG design using individual-level randomization, stratified by the hospital or nursing school. The WCG will receive the digitally supported mindfulness intervention 14 weeks after allocation.

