##### Adherence

Adherence to the instructions for using the digitally supported mindfulness intervention will be operationalized as daily meditation. The frequency of meditation practice (app-based and non–app-based meditation) will be recorded based on the following answer options: several times per day, daily, 4 to 6 times per week, 1 to 3 times per week, less than 1 time per week, or never.

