Attrition bias may occur in individuals with little technical experience. By conducting a web-based survey, individuals with an affinity for technology are more likely to participate in the surveys on an ongoing basis. This restriction cannot be avoided because of pandemic-related regulations. To reduce bias through loss to follow-up (attrition bias), we will send reminder emails of survey participation, and participation in the survey will be incentivized by the intervention provider at one hospital. We will conduct ITT and PP analyses to reduce the risk of misinterpretation of results because of loss to follow-up.

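### The 10-week per-protocol efficacy test uses an adherence rule that the wait-list group cannot meet at T1, so the contrast is undefined or non-randomized

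*Protocol article*

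**What the plan says.** The protocol article separates effectiveness (ITT, all randomized participants) from efficacy, which its introduction defines as the effect seen when the protocol is followed. Under Statistical Methods, Overview: "Efficacy will be evaluated using a per-protocol (PP) approach; only study completers who report adherence will be included in our analyses". The Adherence section defines the criterion: "Adherence to the instructions for using the digitally supported mindfulness intervention will be operationalized as daily meditation".

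For research question 1, each outcome is turned into a T0-T1 difference score, and "we will test whether significant differences exist between the 2 difference scores in the IG and WCG". The next sentence extends this to both samples: "We will perform this for the ITT and PP sample". The Overview sets alpha at .05 for tests involving the primary outcome, with no restriction to the ITT test.

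The Design section states: "The WCG will receive the digitally supported mindfulness intervention 14 weeks after allocation". T1 is at 10 weeks. The adherence row of Table 1 is ticked for both groups at T0, for the IG only at T1, and for both groups at T2 and T3.

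On attrition, Strengths and Limitations says: "We will conduct ITT and PP analyses to reduce the risk of misinterpretation of results because of loss to follow-up".

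**The concern.** The PP rule selects on following the intervention's instructions, but it is applied to a comparison in which one arm has not yet received the intervention and is not asked about adherence. The article states no separate rule for that arm. Selecting on behaviour after randomization in one arm removes the balance that randomization provided.

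Efficacy is half of the stated objective, and the PP test of PSS-10 falls under the .05 alpha wording, so the exploratory label given to the other analyses does not cover it. A difference produced by who chooses to meditate daily could be reported as the effect of the programme when followed. The limitations section does not mention this.

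**Working it through.** **1. Can a control enter the PP sample at T1?** The rule needs a completer who reports daily meditation under the intervention's instructions. There are three ways to apply it to the WCG:

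- *Adherence at T1, literally.* It is not collected in the WCG, which has no access yet. No control is eligible and the two-sample test cannot be computed.
- *Criterion applied to the IG only, all WCG completers kept.* Daily meditators, who chose their own frequency of practice, are compared with controls selected on completion but not on adherence.
- *WCG adherence at T2 or T3.* Membership in a T0-T1 contrast then depends on behaviour after T1 and after crossover.

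The T0 tick does not help, because it precedes the intervention. None of the three gives a randomized contrast.

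**2. The plan's own benchmark.** For d = 0.67, two-sided alpha .05 and power .80, the noncentral t calculation gives 35.96, so 36 per group (power 0.8005). With 20% dropout, 36 / 0.80 = 45 per group. Both stated figures reproduce, so 0.67 can serve as a yardstick.

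**3. Size of the selection effect under the second reading.** The documents give neither an adherence rate nor a correlation between adherence and change, so both are assumed.

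- Completers: 40 and 39 were randomized. With the planned 20% dropout, 40 × 0.80 = 32 in the IG and 39 × 0.80 = 31.2, taken as 31, in the WCG.
- Model: true effect zero. A share q of IG completers is adherent, being those highest on a normal propensity that correlates r with favourable standardized change.
- Spurious difference: d = r × λ(q), with λ(q) = φ(z)/q and z = Φ⁻¹(1 − q). For q = 0.25, z = 0.6745, φ(z) = 0.3178 and λ = 0.3178 / 0.25 = 1.271.

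| q | λ | r = 0.1 | r = 0.2 | r = 0.3 | r = 0.4 |
|---|---|---|---|---|---|
| 25% | 1.271 | 0.13 | 0.25 | 0.38 | 0.51 |
| 30% | 1.159 | 0.12 | 0.23 | 0.35 | 0.46 |
| 40% | 0.966 | 0.10 | 0.19 | 0.29 | 0.39 |
| 50% | 0.798 | 0.08 | 0.16 | 0.24 | 0.32 |
| 70% | 0.497 | 0.05 | 0.10 | 0.15 | 0.20 |

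Simulated rejection rates at nominal 5% (20,000 tests per setting), for r = 0.1, 0.2 and 0.3:

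- q = 30% (10 vs 31): 6.1%, 9.5%, 15.0%
- q = 50% (16 vs 31): 5.7%, 8.0%, 11.9%
- q = 70% (22 vs 31): 5.5%, 6.2%, 7.9%

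At r = 0 there is no bias and rejection is about 5%. In this model a negative r shifts the difference by the same amount against the intervention.

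**The case against.** The strongest reply is that a condensed article commonly leaves an arm-specific PP rule to the full protocol, and that counting wait-list completers as per protocol is ordinary practice because their assigned condition is to wait. That stands to this extent: a missing detail alone would not be a finding. But the article does state a rule, "only study completers who report adherence will be included in our analyses", and applies it to a between-group test that the rule does not fit. The ordinary completion of the rule leads to the second reading above, a non-randomized contrast labelled efficacy.

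Four stronger readings are tempting, and the documents do not support them:

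- *The test is invalid in every case and will favour the intervention.* There is no bias if adherence is unrelated to change in stress. Nurses whose stress is worsening might also meditate more, which would reverse the sign.
- *The controls are wholly unselected.* They must still be completers.
- *Counting practice outside the app is a flaw.* The article says that "The frequency of meditation practice (app-based and non–app-based meditation) will be recorded", and this fits a programme whose workshops teach both kinds of exercise.
- *The article claims that PP analysis by itself reduces attrition bias.* The sentence speaks of ITT and PP together.

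It is also fair that the bias may be small: at 70% adherent and r = 0.1, d is 0.05.

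**Conclusion.** The point holds for the research question 1 PP test only. As stated, its inclusion rule cannot be met by the WCG at T1, and each way of completing it gives either no control arm or a contrast that is not randomized. That contrast is biased unless adherence is unrelated to change in stress. The protocol gives no basis for assuming this and states no adjustment for selection into the adherent set; its planned check of baseline differences addresses whether randomization worked, which is another matter.

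The documents do not fix direction or size. Under the assumed positive correlations of 0.1 to 0.4 and 25% to 70% adherent, the spurious d is about 0.05 to 0.5, from negligible to about three quarters of the planning effect (0.5 / 0.67 = 0.75). The ITT comparison and the sample size are unaffected.

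**What to change.** 1. State the PP rule for each arm, including the time point at which completion and adherence are judged.
2. Report the PP contrast as non-randomized and descriptive, not as a test of efficacy at alpha .05.
3. Base any efficacy statement on a complier-average causal effect: two-stage least squares with randomized group as instrument, adjusted for baseline PSS-10 and the randomization strata. Define uptake in advance from the items under Intensity of Intervention Use (code activation, workshop attendance, workbook use).
4. State its assumptions. Allocation affects stress only through uptake (the exclusion restriction). No WCG member takes up the programme before T1; this needs saying because the app is in public app stores and Table 1 does not show when the use items are asked. Outcome and uptake are covered by the planned multiple imputation for non-responders, since app use is self-reported and not tracked.
5. Reword the attrition sentence in Strengths and Limitations to say that restricting to adherent completers does not protect against loss to follow-up.

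The cost is wording and one extra model, with no new data item if the use items are asked as planned. The downside is precision and meaning. With no WCG uptake, the estimate is roughly the ITT effect divided by IG uptake, so the confidence interval widens by about 1/uptake (1 / 0.70 = 1.4 times at an assumed 70%). It also describes those who took up the programme, not daily meditators.
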